### Ethical Considerations

The study will be conducted in accordance with the principles of the Declaration of Helsinki, the International Council for Harmonisation–Good Clinical Practice (ICH-GCP) Guideline, and the Human Research Act after protocol approval by the regional ethics committee (Ethikkommission Nordwestschweiz: BASEC-ID 2023-02138). Patients will provide written informed consent for the main and the substudy. Data will be collected by specially trained research staff and entered into a password-protected data environment. Each patient will be assigned a study-specific patient identification number (PID). For statistical analysis, datasets will be merged using the PID as an identifier. Upon completion of data collection, including follow-up, patient data will be coded using the PID, and the database will be locked. Coding using the PID will be done at the earliest time point after completion of follow-up data collection. Data generation, transmission, storage, and analysis of health-related personal data will comply with current Swiss legal requirements for data protection and will be performed according to the Human Research Ordinance Art. 5. Health-related personal data captured during this study will remain strictly confidential and will not be disclosed to third parties. Participants will be reimbursed for travel expenses for hospital follow-up visits. No costs will be incurred by participants for taking part in the study.

## Results

The study is in the collection phase. Study recruitment started in February 2024. Data analysis is scheduled to start after all data are collected. As of June 2025, 12 patients have been recruited. Results are expected to be published by the end of 2025.

## Discussion

### What Does the Study Offer?

Because overall diet quality is associated with the risk of frailty, and insufficient protein intake leads to loss of muscle mass and strength [13,14], more attention should be paid to healthy nutrition and adequate protein intake in patients with HF. Although results from other studies suggest that patients with HF may benefit from a high-protein diet, conclusive evidence from prospective controlled clinical trials, particularly in relation to mortality, is scarce. Individual studies, such as a randomized double-blind pilot study in 29 patients with HF, have shown improvements in quality of life after 18 weeks on a high-calorie, high-protein diet [37]. However, most studies on protein intake are observational and have been conducted in the general population [38], while limited data are available for patients with HF. Simpler and more innovative tools for collecting information on protein intake in patients with HF could reduce the burden of long-term home monitoring. Furthermore, such tools may help minimize recall bias, which is particularly problematic in older adults when using retrospective dietary assessment methods. Refrigerator openings could represent such a tool, both in terms of the first opening of the day and overall frequency. For example, a late first refrigerator opening after midnight may be indicative of skipping breakfast. In general, little is known about the nutritional status of older people who skip breakfast, and there are contradictory results regarding meal frequency and frailty [39,40].

To the best of our knowledge, this is the first prospective study investigating the use of refrigerator openings as a potential indicator of protein intake. The use of the refrigerator openings in relation to frailty and sarcopenia would allow easy monitoring. Interventions could be initiated at an early stage and thereby reduce disease progression.

### Limitations

This study has several limitations. First, the patterns of refrigerator openings—regarding time of day and frequency—may be subject to great variations, and the use of single values or combinations of values will require both internal and external validation. Second, the study is limited to patients who live alone. This complicates the generalizability of the results to other populations with HF. The small sample size is based on experience from a previous study, including a similar patient population with hospitalization for HF decompensation. At present, no prior data are available to support a formal power calculation. Third, to verify the accuracy of the refrigerator openings in assessing the protein intake, results must be compared with a standard reference method. This is done in this study with a 24-hour recall. As a retrospective method, it also has weaknesses, in particular, recall bias or unusual eating days. For this reason, at least two 24-hour dietary recalls per person are carried out.

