#### Dietary Assessment

For dietary assessment, food intake will be measured using the 24-hour dietary recall. The 24-hour dietary recall is an open-ended, retrospective dietary assessment method. It aims to record as much detailed information as possible about all foods and drinks consumed by the respondent in the previous 24 hours or the day before [28]. In this study, 24-hour dietary recalls are conducted at 3 different timepoints, at 1 month (optional), 3, and 6 months after hospital discharge. The first 24-hour dietary recall at 1 month is optional, as—unlike the assessments at 3 and 6 months—it cannot be coordinated with a routine follow-up hospital visit. Conducting this assessment would require an additional clinic or home visit, which was deemed burdensome for participants. To reduce participant burden and support adherence, this timepoint was made optional. All 24-hour dietary recalls will be conducted on weekdays by trained dietitians in face-to-face interviews. As the main drawback of this method is the forgetfulness of the participants, the 24-hour dietary recalls will be conducted by using the Automated Multiple-Pass Method (AMPM), as described elsewhere [29]. The AMPM uses multiple memory cues with standardized wording to elicit recall of all possible foods. Before the start of the 24-hour dietary recall, it will be recorded whether the day surveyed reflected a usual day in terms of diet or whether it was an unusual day. A usual day is defined as a day on which the participant ate according to their usual habits and routines, reflecting habitual dietary intake. This terminology was chosen to emphasize the importance of capturing habitual intake patterns. Conversely, an unusual day is determined based on the participant’s own judgment and refers to any day they perceive as not representative of their usual intake. Examples will be provided to participants, for example, holidays, celebrations, excursions, acute illness, or other events that may have significantly altered their eating behavior. The amount of consumed food will be estimated using the photo book of the National Nutrition Survey in Switzerland (menuCH) [30] (Multimedia Appendix 1). The conversion of the estimated amounts into weights will follow the menuCH photo book manuals and commercially available packaging sizes in Switzerland. All conversions will be performed by experienced dietitians. Protein intake in grams (g) and energy intake in kilocalories (kcal) will be calculated using nut.s nutritional software (version 1.33.10 - 2022.08.26; dato Denkwerkzeuge) based on the 24-hour dietary recalls. The nutritional database used in nut.s is adapted for the evaluation of Swiss food products.

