### Statistical Analysis

We will compute the cross-sectional correlations between protein intake (g) and first refrigerator door opening after midnight in minutes (RDmin) at the start (1 month) and at 3 and 6 months (primary outcome). Further, quantities of interest are the correlation between protein intake (g) and refrigerator opening frequency per day (RDfreq), between energy intake (kcal) and RDmin and RDfreq, between (risk of) malnutrition (score) and RDmin and RDfreq, and between HGS (kg) and RDmin and RDfreq. From the time series of refrigerator opening time after midnight in minutes over the period of 6 months, we will create 3 time windows, each window representing the 2-week period prior to each nutrition assessment (Figure 1). For each window, a mean RDmin measurement will be calculated, resulting in 3 RDmin measurements, 3 RDfreq, and 3 measurements of protein intake (g) and energy intake (kcal) from the 24-hour dietary recalls, 3 measurements of malnutrition and HGS (after 1, 3, and 6 months). We will estimate the cross-sectional associations between RDmin and RDfreq and protein intake (g), energy intake (kcal), (risk of) malnutrition (score), and HGS (kg) at 1, 3, and 6 months to quantify the correlation and to assess the stability of this correlation over time. We will compute Spearman correlation coefficients with corresponding 95% CIs.

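### The repeated dietary recalls are offered as the answer to unusual days, but no primary coefficient combines them, so each carries the full day-to-day error of one recall

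*Protocol article*

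**What the plan says.** In Limitations, the protocol article says of the 24-hour recall: "As a retrospective method, it also has weaknesses, in particular, recall bias or unusual eating days". The next sentence gives the remedy: "For this reason, at least two 24-hour dietary recalls per person are carried out".

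Under Dietary Assessment, the schedule is one recall per visit: "24-hour dietary recalls are conducted at 3 different timepoints, at 1 month (optional), 3, and 6 months after hospital discharge". The two guaranteed recalls are therefore those at months 3 and 6. Each is meant to capture "all foods and drinks consumed by the respondent in the previous 24 hours or the day before", that is, one day. Before each recall, "it will be recorded whether the day surveyed reflected a usual day in terms of diet or whether it was an unusual day". The same section says that habitual intake is what matters.

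Under Statistical Analysis, the sensor series is cut into three windows, "each window representing the 2-week period prior to each nutrition assessment". The sensor summary is an average: "For each window, a mean RDmin measurement will be calculated". Protein is not averaged. Each visit's single value enters that visit's own Spearman coefficient with a 95% CI, and these per-visit coefficients are the primary outcome. The Methods paragraph of the Abstract defines it the same way. The stated reason for having several visits is to see whether the correlation is stable over time.

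**The concern.** A second or third recall protects against an untypical day only if the analysis combines recalls within a person. Here the month 3 recall has no influence on the month 6 coefficient, or the reverse. The reason given in Limitations for repeating the recall is therefore not carried through to the primary outcome.

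The pairing is also uneven. Two weeks of averaging take day-to-day noise out of RDmin, while protein keeps all of its own. Independent random error in one variable pulls a correlation towards zero. In a sample of 24, a coefficient shrunk in this way could be read as a sign that refrigerator openings carry little information on habitual protein intake, when part of the weakness comes from using one day of diet.

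**Working it through.** **Side by side.** Limitations: repeats are done because of recall bias and unusual days. Statistical Analysis: one recall per coefficient, coefficients reported visit by visit, no pooling. So the number of recalls behind each primary coefficient is k = 1, whatever the person's total.

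**Inputs from the documents.** n = 24 (Study Design and Participants); one-day recall; two-week sensor mean; Spearman with 95% CI. The plan states no power, precision or target correlation, so it has no figure to reproduce.

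**Assumptions, not in the documents.** λ, the within- to between-person variance ratio of one-day protein intake, is 0.5 to 2. The true correlation between usual protein intake and the window mean of RDmin is 0.5 in absolute value. Usual intake is stable, daily errors are independent, and the distribution is bivariate normal. Only protein is averaged in this illustration.

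**Formulas.** Attenuation factor: f = √(1 / (1 + λ/k)). Attenuated correlation: r = 0.5 × f. Expected Spearman coefficient in a sample of n from a bivariate normal: E = 6 / (π(n + 1)) × [arcsin r + (n − 2) arcsin(r/2)].

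Example for λ = 1, k = 1: f = √(1/2) = 0.707; r = 0.354; E = 6/(25π) × [0.361 + 22 × 0.178] = 0.33.

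| λ (assumed) | k | f | r = 0.5 × f | Expected Spearman, n = 24 |
|---|---|---|---|---|
| 0.5 | 1 | 0.82 | 0.41 | 0.38 |
| 0.5 | 2 | 0.89 | 0.45 | 0.41 |
| 0.5 | 3 | 0.93 | 0.46 | 0.43 |
| 1 | 1 | 0.71 | 0.35 | 0.33 |
| 1 | 2 | 0.82 | 0.41 | 0.38 |
| 1 | 3 | 0.87 | 0.43 | 0.40 |
| 2 | 1 | 0.58 | 0.29 | 0.27 |
| 2 | 2 | 0.71 | 0.35 | 0.33 |
| 2 | 3 | 0.77 | 0.39 | 0.36 |

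Simulation with 24 patients gave the same expected Spearman values to within 0.01. With no error in protein at all, the expected Spearman coefficient is 0.46 rather than 0.50. The loss due to the single-day recall should therefore be counted from 0.46: down to 0.38 at λ = 0.5 and to 0.27 at λ = 2.

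**Gain against precision.** Averaging two recalls raises the expected coefficient by 0.41 − 0.38 ≈ 0.04 (0.414 − 0.378) at λ = 0.5 and by 0.33 − 0.27 = 0.06 at λ = 2. For comparison, take a coefficient of 0.30 at n = 24. On the Fisher z scale, SE = √((1 + 0.30²/2)/21) = 0.223, and the 95% CI is about −0.13 to 0.63.

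**The case against.** - **This is a pilot with no test.** The plan promises coefficients and confidence intervals, with no significance level or power target. That stands, so significance or power figures are not used here as a criterion. Purely random error in protein also pulls towards zero and does not manufacture an association.
- **The gain is small beside the sampling error.** This stands too. A rise of 0.04 to 0.06 is minor against an interval of that width, and sample size drives the imprecision more than the number of recalls does. The gain does, however, come from data already planned.
- **The repeats have a use.** A reader might infer that they serve no purpose. The documents do not support that: they serve the stated aim of judging stability over time. What they do not do is reduce error in any one coefficient.
- **Pooling is not a cure for recall bias.** A reader might infer that averaging would deliver everything Limitations claims. It would not. Averaging reduces random daily variation and dilutes unusual days, but consistent under-reporting stays. Forgetfulness is dealt with separately, by the multiple-pass interview.
- **Unused flag and no same-day pairing.** A reader might count these as omissions. An article may leave such details to the full protocol or analysis plan, and a two-week mean is a defensible choice when habitual behaviour is the target. They are not faults here.
- **The primary outcome should be replaced.** This is also tempting, but the per-visit coefficients answer a stated question. An analysis plan that is not shown could add a pooled estimate; it could not substitute one without changing the published primary outcome.

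**Conclusion.** The mismatch holds on the article's own text. Limitations credits the repeats with a protection that the Statistical Analysis section does not apply, and every primary coefficient is expected to be attenuated. The direction follows from the design, given random daily error that is independent of the sensor. The size does not: it rests on an assumed variance ratio of 0.5 to 2, giving a multiplier of about 0.82 to 0.58 with one recall against 0.89 to 0.71 with two, and on stable usual intake over the months between recalls. If habitual intake drifts as patients recover, the benefit of pooling would be smaller. Severity: should fix.

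**What to change.** **Statistical Analysis.** Keep the per-visit Spearman correlations for the stability aim. Add one pre-specified pooled Spearman correlation between each person's mean protein over the available recalls (months 3 and 6, and month 1 where done) and that person's mean RDmin over the matching windows. Take the 95% CI from a bootstrap that resamples patients. State that the overall conclusion about habitual protein intake rests on this estimate. As a sensitivity analysis, repeat it without recalls that the participant flagged as unusual days.

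**Limitations.** Say that pooling the repeats reduces random day-to-day variation and dilutes unusual days, that it does not remove systematic recall bias, and that the per-visit coefficients are expected to be attenuated.

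**Cost.** A few sentences and a few lines of code, with no new data. Analysis is due to start only after data collection is complete, so the addition can still be pre-specified. The downsides are small and should be stated: the pooled estimate describes average intake over months, assumes roughly stable habitual intake, and mixes people with two and three recalls, whose means differ in error, because month 1 is optional.

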### Conclusions

This study aims to provide new insight into the relation between refrigerator openings and nutritional intake, particularly protein intake. It is hypothesized that monitoring refrigerator openings within the framework of an ambient sensor system may help identify patients at risk for malnutrition and, as a result, for muscle mass and strength loss. Such identification of insufficient, and particularly protein-deficient, diets could enable simple monitoring and timely intervention to prevent or at least delay sarcopenia and frailty. This, in turn, may improve quality of life and potentially reduce health care costs. In addition, this low-effort monitoring approach could be of interest for other target groups.

## Appendix

Multimedia Appendix 1 Examples from the photo book of the national nutrition survey in Switzerland (menuCH).

## Abbreviations

AMPM: Automated Multiple-Pass Method
HF: heart failure
HGS: hand grip strength
ICH-GCP: International Council for Harmonisation–Good Clinical Practice
menuCH: National Nutrition Survey Switzerland
MNA: Mini Nutritional Assessment
MNA-SF: Mini Nutritional Assessment Short Form
PHQ-9: 9-item Patient Health Questionnaire
PID: patient identification number
RDfreq: refrigerator door opening frequencies per day
RDmin: refrigerator door opening after midnight in minutes
